In this multicenter, prospective cohort study, we aim to use the *Baidu Jieduan Granule* combined with Western medicine to dynamically observe the changes of patient's blood, cytokines, coagulation function, chest computed tomography (CT), respiratory distress (respiratory rate, RR), blood oxygen saturation, oxygenation index, and patient prognosis (healing, worsening, and death),to prove the clinical efficacy of *Baidu Jieduan Granule* in curing COVID-19, to reveal the possible mechanism from the immune route, and to evaluate the safety. We will also assess mental health outcomes through our 1 year follow-up.

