### Objectives

2.2

The main aim of our trail is to investigate the efficacy and safety of *Baidu Jieduan Granule* in the common type of COVID-19 patients and assess mental health outcomes through our 1year follow-up.

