#### Primary outcomes

2.10.1

The primary outcomes of our study are clinical outcomes. In our study, there are 4 kinds of clinical outcomes:

1.recovery, the following conditions shall be met:1.the body temperature is normal for 3 consecutive days2.respiratory symptoms disappeared completely,3.the nucleic acid test of respiratory tract samples is negative for 2 consecutive times (the sampling interval is at least 1 day);2.condition improved, meet any of the following 2 items:1.the clinical symptoms are significantly relieved,2.the nucleic acid of sputum, nasopharynx test paper and other respiratory tract samples are negative for 2 consecutive times (the sampling interval should be at least 24 hours);3.condition worsen, one of the following situations occurs:1.shortness of breath, respiratory rate (RR) ≥30 times/minutes,2.oxygen saturation ≤93% in resting state,3.arterial oxygen partial pressure (PaO2) / fraction of inspired oxygen (FiO2) ≤300 mm Hg,4.shock,5.respiratory failure, requiring ventilator support,6.organ failure needing intensive care, and7.death.

We count the number of patients of each kind of clinical outcomes then calculate the ratio.

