### Statistical analysis

2.12

Statisticians from coordination center will oversee this work. We analysis all data sets by IBM SPSS Statistics 24.0 software. We express collected data by mean ± standard deviation or median and interquartile distance. The comparison between groups of measurement data which accorded with normal distribution and homogeneous variance is *t*-test. At the same time, the nonparametric test is used for non-compliance with a normal distribution. Chi-Squared test will be used to compare the count data or rate, and the logistic test to compare the survival rate between groups. P value <.05 is considered as statistically significant.

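### The only listed test that fits the graded primary outcome is a chi-squared test, which ignores the order of the categories; on the three listed categories it costs about 10 points of power under an assumed common odds ratio of 1.8

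*Protocol article*

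**What the plan says.** Section 2.10.1 makes clinical outcome the primary outcome. It states "In our study, there are 4 kinds of clinical outcomes" but numbers three: recovery, condition improved and condition worsen. Death appears as the last item under worsen. The summary is "We count the number of patients of each kind of clinical outcomes then calculate the ratio".

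Section 2.12 assigns tests by type of data and does not mention the primary outcome by name:

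- Measurement data get a t-test, and "the nonparametric test is used for non-compliance with a normal distribution".
- For categorical data, "Chi-Squared test will be used to compare the count data or rate".
- Survival gets its own method: "the logistic test to compare the survival rate between groups".
- The threshold is "P value <.05 is considered as statistically significant". Sidedness is not stated.

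The purpose is directional. The Introduction wants "to prove the clinical efficacy of" the granule, and section 2.2 sets out to "investigate the efficacy and safety of" it. No category or cut-point is named as the one that decides efficacy.

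**The concern.** The outcome runs from best to worst, and the claim to be supported is that patients given the granule end up nearer the better end. The chi-squared test can be applied in two ways, and section 2.12 does not say which.

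- **One test on the whole 2×K table.** The null is that the two distributions are identical, and the alternative is any difference at all. If benefit is spread over the categories, ignoring their order wastes power. A significant result can also come from a pattern in which more patients recover and more worsen.
- **One test per category.** There are then three or four primary comparisons, each at .05, with no rule for which one counts. The middle category has no clear direction: a higher improved rate is good if those patients would otherwise have worsened, and bad if they would otherwise have recovered.

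This would remain a problem with perfectly comparable groups. It is separate from confounding by the non-random grouping.

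**Working it through.** **Inputs from the article.** 300 patients (2.3, 2.7), allocation 1:1 (2.8), withdrawal about 10% (2.7), threshold .05 (2.12; taken as two-sided). The plan has no power figure to reproduce, because 2.7 says the sample size could not be calculated. The arithmetic it does give is consistent: 4 × 75 = 300. After withdrawal, 300 × 0.9 = 270, or 135 per group.

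**Assumptions.** Control category rates, and a common odds ratio of 1.8 toward better outcomes. Neither is in the protocol.

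**Step 1: order is ignored.** Take an illustrative table of recovery/improved/worsen, 68/47/20 against 54/50/31 (135 each).

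- Pearson: the column totals are 122, 97 and 51, so the expected counts per group are 61, 48.5 and 25.5. Then χ² = 2 × (7²/61 + 1.5²/48.5 + 5.5²/25.5) = 4.07 on 2 df, P = 0.13. This is a sum over columns, so it is the same whatever order the categories are put in.
- Wilcoxon with ties: the midranks are 61.5, 171 and 245. The rank sum is 68 × 61.5 + 47 × 171 + 20 × 245 = 17,119, against an expected 135 × 271/2 = 18,292.5. The tie-corrected SD is 593.1, so z = −1.98, P = 0.048.

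**Step 2: power.** The treated rates come from multiplying each cumulative odds by 1.8. Example, control 50/30/20: cumulative odds 1 and 4 become 1.8 and 7.2, the cumulative rates become 64.3% and 87.8%, and the treated rates are 64.3/23.5/12.2. Simulated power at 135 per group (200,000 replicates):

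| Control rates (%) | Chi-squared, whole table | Rank (ordinal) test | 2×2 on recovery only |
|---|---|---|---|
| 50/30/20 | 59% | 69% | 67% |
| 60/25/15 | 53% | 64% | 62% |
| 40/30/30 | 63% | 73% | 66% |
| 50/30/10/10 | 52% | 70% | 67% |
| 60/25/5/10 | 46% | 64% | 62% |
| 40/30/20/10 | 56% | 73% | 66% |

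The loss against the ordinal test is about 10 points with three categories and about 17 with four. The noncentrality needed for 80% power shows the same thing: 7.85 on 1 df, 9.63 on 2 df and 10.90 on 3 df. The ratios are 9.63/7.85 = 1.23 and 10.90/7.85 = 1.39, so the whole-table test needs about 23% or 39% more patients for the same effect.

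**Step 3: significant is not the same as better.** Take control 45/45/10 and treated 55/25/20: more recovery, but twice the worsening. The chance that a treated patient does better than a control, counting ties as half, is 0.55 × (0.55 + 0.225) + 0.25 × (0.10 + 0.225) + 0.20 × 0.05 = 0.5175, which is close to even. The whole-table chi-squared test rejects in 93% of studies and the rank test in 9%.

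**Step 4: error rates with no effect.** The whole-table chi-squared and the rank test both reject in about 5%. With a separate 2×2 test on each category, at least one P<.05 occurs in about 12% (three categories) or 17% (four).

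**The case against.** **The assignment is inferred.** Section 2.12 is a generic list and never says which test the primary outcome gets. The article is condensed, and the fuller analysis plan is not shown. That is true. Still, counts and ratios per category match the chi-squared sentence, and none of the other listed tests fits. The point is therefore about a method the article names, not about missing detail.

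**Four ordered levels are not listed.** A reader who relies on the stated number would quote a loss of 17 points. The text lists only three categories, and on those the loss is about 10.

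**A single 2×2 test on recovery has a direction and loses little.** This is the strongest objection. In the table above the loss against the rank test is only 2 to 7 points. If recovery had been named as the deciding category, the power argument would be minor. It is not named.

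**The mixed-effect example favours the rank test.** This is largely right. A net effect near even is close to the rank test's own null, so its low rejection rate is nearly built in. The chi-squared test is correct that the distributions differ; the mistake would be to call that efficacy. An ordinal test on its own would also tend to miss a doubled worsening rate, so it needs the worsen proportion beside it.

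**No validity fault.** A reader might infer that the planned test inflates false positives, or that it breaks a power claim. Neither follows: the whole-table test holds 5%, and the protocol states no power. Only undirected category-by-category testing raises the error rate, and the article does not say that this is intended.

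**Conclusion.** The concern holds as one of efficiency and interpretation. The test that fits the primary outcome disregards its order, while the aim is directional. Under a common odds ratio of 1.8 and 135 per group, the whole-table test loses about 10 points of power on the three listed categories, and about 17 if a fourth is intended. Its P value alone cannot support a claim of better outcomes. Tested category by category with no deciding category, the chance of some significant primary result under no effect is about 12% to 17%.

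All of these sizes rest on assumed rates, and the power losses also on a similar shift at every cut. For an effect confined to one middle category, or otherwise not monotone, the chi-squared test can be the more sensitive one. The documents do not show that the planned test is invalid, that four disjoint levels exist, or that several co-primary tests are planned.

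**What to change.** 1. **Section 2.10.1.** Reconcile the categories first, so that they are mutually exclusive, ordered and equal in number to the stated count. At present four are announced and three numbered. Two negative nucleic acid tests are enough for improved and are also required for recovery, so a recovered patient meets both. Death sits inside worsen. No ordinal model can be fitted until this is settled.
2. **Section 2.12.** Name one ordinal analysis for the primary outcome: proportional-odds logistic regression carrying the matching factors in 2.8 (gender, age, basic diseases), reported as a common odds ratio with 95% CI. Its unadjusted form is the Wilcoxon-Mann-Whitney test. State that the efficacy conclusion rests on this result and its direction.
3. **Reporting.** Give counts and percentages per category as description, with the worsen proportion and its CI alongside, so that opposite shifts are visible.

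The cost is a clarified definition and about one sentence on analysis. No new type of data is needed, and ordinal regression is available in the SPSS version named in 2.12. Section 4.1 places the study already in follow-up, so the change should be dated and recorded as made before outcomes are compared by group, or else labelled post hoc. The main downside is the assumption of a similar shift at each cut, which the per-category table lets readers judge. The change does not address confounding from the non-random grouping beyond the factors in the model.

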### Grouping

2.8

Three hundred COVID-19 cases aged 18 to 80 years are assigned into 2 groups (experimental group and control group) basing on whether they use *Baidu Jieduan Granule* at a ratio of 1:1. The experimental group and the control group are paired with gender, age and basic diseases so that they are comparable.

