### Data collection and management

2.14

We design the case report form (CRF) table as it presented in Additional file 5 by our study protocol. After collecting the information of patients, we will complete the CRFs rightly and timely. Then we input and organize them into an excel sheet. Finally, we will hand it over to statistical experts who will perform statistical analysis. The units of measurement should be unified. We will keep the personal and medical information of all patients strictly confidential. Statistical analysis results will be presented by publishing articles in professional journals or websites after finishing this study. The study procedure and assessments flowchart are as Table 1.

**Table 1 T1:** Study procedure and assessment.

		Observation node					Follow-up phase				
Study period	Visiting items	D1	D3	D5	D7	D14			1 year		
Screening stage	Inclusion criteria	X									
	Signing informed consent	X									
	Exclusion criteria	X									
	Matching and distribution	X									
Observation stage	Administration of study drug	X	X	X	X	X					
	Demographic	X									
	General Condition	X									
	Primary disease	X									
	Complication	X									
	Vital signs	X	X	X	X	X					
	Oxygenation index	X	X	X	X	X					
	Oxygen saturation	X	X	X	X	X					
	Chest CT	X		X		X					
	Hepatic function	X	X	X	X	X					
	Renal function	X	X	X	X	X					
	Cardiac function	X	X	X	X	X					
	Inflammatory indicators	X	X	X	X	X					
	Coagulation function	X	X	X	X	X					
	APACHEII score	X	X	X	X	X					
	Adverse event recording	X	X	X	X	X					
	Drug delivery/taking back/ destruction	X	X	X	X	X					
	Clinical outcomes					X					
	Safety evaluation	X	X	X	X	X					
Follow-up phase	LSAs								X		
	DASS21								X		

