It is inspiring that lots of clinical trials are conducted and reported to evaluate the efficacy of TCM in treating SARS-CoV. However, most of them are poorly designed and lack of persuasion. In our multicenter prospective cohort study, *Baidu Jieduan Granule* we used is under the guidance of the theory “ Internal and External Relieving -Truncated Torsion ” and take the clinical characteristics of COVID-19 patients into consideration. By observing the changes in various indicators and imaging examination results during the disease, we seek to reveal the effectiveness and possible mechanism of *Baidu Jieduan Granule* in the treatment of COVID-19 using statistical analysis. Meantime, we expect to observe the safety and long-term mental health outcomes through follow-up.

This study has several limitations. First, we do not adopt randomized controlled clinical trials. Second, we only involve the common type of COVID-19 patients. Third, our follow-up time is not long enough.

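### The stated chi-squared and t-tests leave a non-randomised comparison, matched only on gender, age and underlying disease, unprotected against confounding by baseline severity and centre

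*Protocol article*

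**What the plan says.** Section 2.8 (Grouping) has patients "assigned into 2 groups (experimental group and control group) basing on whether they use" the granule, at 1:1. The same section gives the one measure meant to make the groups alike: "The experimental group and the control group are paired with gender, age and basic diseases so that they are comparable". Table 1 in section 2.14 schedules a step called "Matching and distribution" on D1. Neither place says whether this is individual pairing or frequency matching.

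The Discussion (section 3) lists as a limitation: "First, we do not adopt randomized controlled clinical trials". It offers no analytic remedy. Section 2.1 names four centres, three in Hubei and one in Shanghai.

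The primary outcome (section 2.10.1) is a set of clinical outcome categories, reported as counts and ratios. Section 2.12 assigns a test to each kind of data:

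- Counts and rates, which include the primary outcome: "Chi-Squared test will be used to compare the count data or rate".
- Continuous data: a t-test where the data meet the condition in "The comparison between groups of measurement data which accorded with normal distribution and homogeneous variance", and otherwise a nonparametric test.
- Survival: "the logistic test to compare the survival rate between groups", with no covariates stated.

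The section names no covariate, stratification, propensity or matched-pair method. The significance level is 0.05.

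**The concern.** The Introduction states a causal aim: to prove that the granule works. Without randomisation, users and non-users can differ at entry in how ill they are and in which hospital treats them. Both can plausibly affect the day-14 outcome. The worsening category itself uses respiratory rate, oxygen saturation and the oxygenation index.

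Matching covers neither factor, and the named tests adjust for neither. Followed as written, a difference in case mix between the groups would be reported as a difference between treatments, with a P value that reflects sampling error only.

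A second, smaller question concerns the matching. If patients are individually paired, ordinary chi-squared and two-sample t-tests ignore the pairs.

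**Working it through.** **The plan's own figure.** Section 2.7 says an exact sample size could not be calculated, and gives no power, effect size, rate or SD. The total of 300 can be checked only for consistency: 4 centres × 75 = 300, and 1:1 allocation gives 150 per group.

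**Step 1: what is controlled.**

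| Factor | Matched (2.8) | Adjusted (2.12) | Measured on D1 (Table 1) |
|---|---|---|---|
| Gender, age, underlying disease | yes | no | yes |
| APACHE II, CT score, oxygenation | no | no | yes |
| Centre | no | no | known for every patient |

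**Step 2: severity imbalance with an ineffective drug.** The inputs are assumptions, because the documents give none: recovery 75% in milder and 45% in sicker patients, whichever group they are in. The calculation reduces the outcome to recovered or not. With m the share of milder patients in a group, the expected recovery rate is p = 0.75m + 0.45(1 − m) = 0.45 + 0.30m.

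The rejection rate of the two-sided 5% test with n = 150 per group is Φ[(d − 1.96·SE0)/SE1] + Φ[(−d − 1.96·SE0)/SE1]. Here d = p1 − p2, SE0 = √(2p̄(1 − p̄)/n) and SE1 = √([p1(1 − p1) + p2(1 − p2)]/n). In every row p̄ = 0.615, so SE0 = √(2 × 0.615 × 0.385/150) = 0.0562.

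| Milder share, users v non-users | p1 v p2 | Spurious difference | Rejection rate |
|---|---|---|---|
| 55% v 55% | 61.5% v 61.5% | 0 points | 5.0% |
| 60% v 50% | 63.0% v 60.0% | 3 points | 8.3% |
| 65% v 45% | 64.5% v 58.5% | 6 points | 18.7% |
| 70% v 40% | 66.0% v 57.0% | 9 points | 36.0% |

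Swapping the groups reverses the sign. If sicker patients tend to receive the granule, the same spurious difference counts against it and could mask a real benefit.

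**Step 3: centre imbalance with an ineffective drug.** Assume recovery of 60, 70, 80 and 90% at four centres of 75 patients each.

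- Half of each centre treated: no bias, 5% rejection.
- Treated shares 40/45/55/60%: 76.7% v 73.3%, a spurious 3.5 points (before rounding), 10.8% rejection.
- Treated shares 30/40/60/70%: 78.5% v 71.5%, a spurious 7 points, 28.7% rejection.

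The overall 1:1 ratio holds in all three cases, so it does not by itself secure balance within centres.

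**Step 4: ignoring pairs, if pairs exist.** With within-pair correlation ρ (assumed), the unpaired standard error is 1/√(1 − ρ) times the paired one, and the actual two-sided level is 2[1 − Φ(1.96/√(1 − ρ))].

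| ρ | SE ratio | Actual level |
|---|---|---|
| 0.1 | 1.054 | 0.039 |
| 0.2 | 1.118 | 0.028 |
| 0.3 | 1.195 | 0.019 |

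A simulation of t-tests on 150 pairs agrees: the unpaired test rejected 2.6% of the time at ρ = 0.2 and 1.8% at ρ = 0.3. The paired test rejected 4.8% and 4.4%. The error is therefore conservative: it costs power and does not create false positives.

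**The case against.** The strongest reply is that the article condenses a fuller plan and that a covariate list belongs in a statistical analysis plan. That holds for the exact list. It does not dispose of the point, because section 2.12 is not silent: it assigns a test to each type of data, the primary outcome included, and none of those tests adjusts for anything. The logistic method is limited to survival, with no covariates stated.

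A reader might infer that the treatment effect is confounded by severity and centre. The documents do not support that as fact. They report no imbalance. Enrolment is limited to the common type, several serious diseases are excluded, and three factors are matched. All of this narrows the scope for bias without removing it: the plan still measures severity on scales that can vary within the common type.

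A reader might also infer that pairs are wrongly analysed as independent, so that the error estimates are wrong. That requires individual matching, which section 2.8 does not establish. The unpaired form of the tests is itself an inference, although a reasonable one from the equal-variance condition and the plain chi-squared test. Even with individual pairs, the effect is conservative and secondary.

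Three cautions about the remedy also stand:

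- A long covariate list may overload the model if worsening is uncommon.
- Conditional logistic regression would use only outcome-discordant pairs. With 10% independent withdrawal, 1 − 0.9² = 19% of pairs would lose a member.
- D1 is not shown to be before treatment. Table 1 gives study drug on D1, while section 2.10.2 refers to d0 for coagulation and for the APACHE II improvement rate.

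**Conclusion.** The point holds in this form: the analysis fixed in section 2.12 does not protect a non-randomised comparison against confounding by baseline severity or centre, and the matching in section 2.8 does not fill the gap. A significant crude result could not be told apart from patient or centre selection, so the point must be fixed before the study is used to claim efficacy.

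The size and direction of any bias are unknown. The rejection rates of about 5% to 36% rest wholly on the assumed recovery rates and severity imbalances, and the centre figures likewise; with balanced groups there is no bias. The pairing question is minor and depends on the type of matching.

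**What to change.** 1. Make the primary analysis a pre-specified logistic or proportional-odds model of the day-14 outcome on group. Adjust it for centre, a short list of baseline severity measures (for example APACHE II, CT score and oxygenation) and the matching factors.
2. Require the severity values to precede the first dose in users and to come from a corresponding time point in non-users. Reconcile the d0 and D1 references so that this can be verified.
3. Use the same adjustment for continuous outcomes. Keep the crude chi-squared, t and nonparametric tests as descriptive.
4. State whether matching is individual or by frequency. If individual, keep the pair identifier and use pair-clustered (robust or GEE) standard errors, which also retain patients whose partner withdrew. If by frequency, adjustment for the matching factors is enough.

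The cost is some degrees of freedom, revised wording and modest programming. The severity measures are already scheduled on D1 and centre is known, so no new data are needed provided the D1 values prove to be pre-treatment. Section 4.1 says the study is already in follow-up, so the model should be fixed before outcomes are compared by group. If that is no longer possible, its timing should be disclosed. Adjustment does not remove confounding by factors that were not measured, so the stated limitation should remain.
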